**Sample size**

The sample size of AGYW who will participate in the interviews and provide biomarker samples at Time 1 is 350. Interviews will be repeated after 3 to 4 months for all participants, and biomarkers collected again for those who continue in the PrEP program. Assuming a continuation rate of 40% (and 10% loss to follow up), we expect to collect 175 repeated DBS samples, for a total of 525 samples.

PrEP Adherence at each time point will be primarily measured by the percentage of AGYW whose PrEP drug levels in dried blood spots reached a certain threshold reflecting the exposure to PrEP drug in the recent past. Specifically, PrEP adherence will be measured by the percentage of AGYW whose tenofovir-diphosphate drug levels in DBS exceeds 30f/molx106, which is consistent with an average of at least four PrEP doses per week.

Assuming a discontinuation/ loss to follow-up rate of 50%, and a two-level factor (potentially associated with PrEP adherence), this sample size will allow us to detect cross-sectionally at the first time point a minimum absolute difference of 15% in the PrEP adherence rates between the levels of the factor at 80% power given a type I error rate of 5% and a two-sided test (Table 3).

**Table 3.** Sample size and power considerations for AGYW interview and DBS samples

| **Absolute difference in adherence rates** | **Sample size needed to measure the absolute difference in the adherence rates** | |
| --- | --- | --- |
|  | **80% power** | **90% power** |
| 25% | 136 | 178 |
| 20% | 206 | 270 |
| 15% | 350 | 462 |
| 10% | 752 | 992 |

Table 4 presents the two-sided 95% confidence intervals for the true PrEP adherence rates at the two time points (for DBS sample and interviews) for a discontinuation/loss to follow-up rate of 30% or 50%. For example, there is a 95% chance that the true PrEP adherence rate at Time point 1 is in the range (44.76%, 55.24%) if the observed adherence rate is 50% at this time point. Moreover, assuming a discontinuation/loss to follow-up rate of 50%, there is a 95% chance that the true PrEP adherence rate at Time point 2 will lie in (23.21%, 36.79%) if the observed adherence rate is 30% at Time point 2. Furthermore, the 95% confidence intervals for the absolute difference in the PrEP adherence rates between the two visits are also shown in Table 4. For example, the absolute difference in the true PrEP adherence rates between Time point 1 and Time point 2 will be in the range (11.85%, 28.15%) with a probability of 0.95 if the observed adherence rates are 50% and 30% at Time points 1 and 2, respectively, assuming a discontinuation/loss to follow-up rate of 50% and a correlation of 0.1 between the adherence measures at the two time points.

**Table 4:** 95% confidence intervals for the true PrEP adherences given by possibly observed PrEP adherence rates at the two time points.

| **95% CI for true the PrEP adherence based on the observed PrEP adherence rates by visit** | | | | |
| --- | --- | --- | --- | --- |
| **Time point 1** | | **Time point 2** | | |
| **Observed PrEP adherence rate** | **95% CI for the true PrEP adherence rate** | **Observed PrEP adherence rate** | **95% CI for True PrEP adherence rate** | |
|  |  |  | **30% discontinuation/ loss to follow-up** | **50% discontinuation/ loss to follow-up** |
| 30% (Low) | (25.2%, 34.8%) | 10% | (6.24%, 13.76%) | (5.56%, 14.44%) |
|  |  | 20% | (14.99%, 25.01%) | (14.07%, 25.93%) |
| 50% (Medium) | (44.76%, 55.24%) | 30% | (24.26%, 35.74%) | (23.21%, 36.79%) |
|  |  | 40% | (33.87%, 46.13%) | (32.74%, 47.26%) |
| 70% (High) | (65.2%, 74.8%) | 50% | (43.74%, 56.26%) | (42.59%, 57.41%) |
|  |  | 60% | (53.87%, 66.13%) | (52.74%, 67.26%) |
| **95% CI for the absolute difference in the true PrEP adherence rates between the two visits** | | | | |
| **Observed PrEP adherence ratet Visit 1** | **Observed PrEP adherence rate at Visit 2** | | **30% discontinuation/ loss to follow-up** | **50% discontinuation/ loss to follow-up** |
| **CORR=0.1** | | | | |
| 30% (Low) | 10% | | (14.21%, 25.79%) | (13.79%, 26.21%) |
|  | 20% | | (3.42%, 16.58%) | (2.76%, 17.24%) |
| 50% (Medium) | 30% | | (12.63%, 27.37%) | (11.85%, 28.15%) |
|  | 40% | | (2.34%, 17.66%) | (1.48%, 18.52%) |
| 70% (High) | 50% | | (12.5%, 27.5%) | (11.58%, 28.42%) |
|  | 60% | | (2.6%, 17.6%) | (1.71%, 18.29%) |
| **CORR=-0.1** | | | | |
| 30% (Low) | 10% | | (13.61%, 26.39%) | (13.14%, 26.86%) |
|  | 20% | | (2.72%, 17.28%) | (2.01%, 17.99%) |
| 50% (Medium) | 30% | | (11.85%, 28.15%) | (11.02%, 28.98%) |
|  | 40% | | (1.54%, 18.46%) | (0.63%, 19.37%) |
| 70% (High) | 50% | | (11.74%, 28.26%) | (10.78%, 29.22%) |
|  | 60% | | (1.84%, 18.16%) | (0.91%, 19.09%) |

Note: CORR denotes the correlation between the two adherence measures.

For the qualitative component, we plan to conduct two focus groups with AGYW peers who are not participating in the PrEP program, two focus groups with Safe Space mentors, and two with health providers, and each group will have 8 to 10 participants. Hence the estimated total sample size is 48 – 60 focus group participants.

For the qualitative interviews with PrEP continuers and discontinuers, a sample size of 16 AGYWs of each type, is considered sufficient to achieve saturation on the themes of interest.^[[47]](#endnote-47)^ The PrEP continuers will be randomly selected to participate in in-depth interviews from among the survey respondents who continue with PrEP, while the discontinuers will be randomly selected from among survey respondents who have discontinued PrEP.

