### 4.0 Study procedures

The study procedures involve two one-on-one semi-structured interviews conducted by study staff with the AGYW. These interviews will take not more than 1 hour. The interviews will take place at private spaces in the DREAMS program ‘safe spaces’ or, if preferred by participants, may alternatively be conducted at other community locations, places of residence or the workplace as convenient and desired by the participant.

We will conduct one follow-up visit with each AGYW after an interval of 3 to 4 months. At this visit study staff will conduct a second interview. If the AGYW is continuing with PrEP, questions will focus on adherence and factors that impact adherence. If the AGYW has discontinued PrEP, questions will focus on reasons for discontinuation. Illustrative lines of inquiry for both interviews are outlined below.

We will collect a dried blood spot (DBS) sample from each AGYW who is continuing in the PrEP program at two points in time, separated by an interval of 3 to 4 months. PrEP discontinuation is defined as 60 or more days since due for a PrEP refill, and AGYW reports that she is not currently taking PrEP. Those who have discontinued will participate in the interview only.

A trained HTS (HIV testing services) worker -- trained in research ethics, blood sampling via fingerstick, and interviewing techniques -- will be employed as study staff to take the samples and conduct the interviews.

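### Table 4 compares adherence in all 350 women at Time 1 with adherence only in those still on PrEP at Time 2, so the between-visit difference mixes selection with change.

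*Protocol*

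**What the plan says.** Section 3.0, Sample size, fixes the Time 1 denominator: "The sample size of AGYW who will participate in the interviews and provide biomarker samples at Time 1 is 350". For the second visit it says: "Interviews will be repeated after 3 to 4 months for all participants, and biomarkers collected again for those who continue in the PrEP program". Section 4.0 adds: "Those who have discontinued will participate in the interview only". It also gives the rule for stopping: "PrEP discontinuation is defined as 60 or more days since due for a PrEP refill, and AGYW reports that she is not currently taking PrEP".

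The endpoint is a proportion of women above a DBS drug-level cut-off: "PrEP Adherence at each time point will be primarily measured by the percentage of AGYW whose PrEP drug levels in dried blood spots reached" the stated threshold. The protocol does not say whether a woman who has stopped PrEP belongs in the Time 2 denominator. On numbers it says: "we expect to collect 175 repeated DBS samples, for a total of 525 samples".

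Table 4 and its text then give a between-visit comparison. For observed rates of 50% and 30%, "the absolute difference in the true PrEP adherence rates between Time point 1 and Time point 2 will be in the range (11.85%, 28.15" (the printed pair is 11.85% to 28.15%), "assuming a discontinuation/loss to follow-up rate of 50% and a correlation of 0.1 between the adherence measures at the two time points". The Data analysis text names kappa, sensitivity and specificity, chi-square tests and multivariate regression. It neither restricts the Time 1 rate to continuers nor assigns an adherence value to women who stopped.

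**The concern.** The two rates in the difference describe different groups: everyone on PrEP at enrolment, and those who remained 3 to 4 months later. By the protocol's own planning figure, half the women have no Time 2 sample. If women with low drug levels stop more often, the Time 2 rate is a rate among survivors and lies above what the same women would show by comparison with themselves. If high adherers stop more often, the bias runs the other way.

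The Study design section gives assessment of adherence and persistence over time as the reason for repeating the interview and the DBS. A difference that moves when nobody's adherence has changed does not serve that purpose.

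**Working it through.** **1. Reproduce the printed interval.** Inputs from Sample size and Table 4: n1 = 350, n2 = 175 (50% loss), p1 = 0.50, p2 = 0.30, correlation r = 0.1.

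- SE1 = √(0.50 × 0.50 / 350) = 0.02673
- SE2 = √(0.30 × 0.70 / 175) = 0.03464
- Variance of the difference = SE1² + SE2² − 2r·SE1·SE2 = 0.000714 + 0.001200 − 0.000185 = 0.001729
- Half-width = 1.96 × √0.001729 = 8.15 points, giving 11.85% to 28.15%, as printed.

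The other difference rows reproduce to within 0.01 point with n2 = 175 or 245, apart from one limit (step 5). So the table compares 350 women with the remaining 175 or 245.

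**2. The same women at both visits.** With 175 at each visit, SE1 = √(0.25 / 175) = 0.03780. The variance is 0.001429 + 0.001200 − 0.000262 = 0.002367 and the half-width 9.53 points, giving 10.47% to 29.53%. This does not match the printed interval, so Table 4 is not a paired comparison. For 50% against 40%:

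| Correlation | Table 4 (350 vs 175) | 175 pairs |
|---|---|---|
| 0.1 | 1.48% to 18.52% | 0.16% to 19.84% |
| −0.1 | 0.63% to 19.37% | −0.88% to 20.88% |

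**3. Size of the selection effect (assumed rates).** The protocol gives no adherence rates by continuation status. Assume 50% adherent at Time 1, 40% stopping, non-adherent women twice as likely to stop, and no other change.

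- 0.5x + 0.5(2x) = 0.40, so x = 0.267 of adherent and 0.533 of non-adherent women stop.
- Adherent share of continuers = 0.5 × 0.733 / 0.6 = 61.1%.
- The contrast reads 50% to 61%. The paired change is zero.
- At a risk ratio of 3, x = 0.20 and the share is 0.5 × 0.8 / 0.6 = 66.7%, a spurious rise of 16.7 points. At a ratio of 1 there is none.

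The 40% stopping rate is an assumption. The protocol prints 40% as a continuation rate, but 350 × 0.40 = 140. Its 175 samples need 50% remaining, for example 40% stopping plus 10% lost.

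Using odds ratios between Time 1 adherence and continuing, over Time 1 rates of 30% to 70% and continuation of 40% to 70%, the spurious rise is about 4 to 10 points at an odds ratio of 2 and 7 to 20 points at 4.

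**4. Can the sign reverse?** Take 50% adherent at Time 1, half continuing, and an odds ratio of 4. Continuers were then 66.7% adherent at Time 1 and the others 33.3%. Let continuers fall to 60%. Their true change is 60 − 66.7 = −6.7 points. The plan's contrast is 60 − 50 = +10 points, and its own formula (r = 0.1) gives +1.48 to +18.52, which excludes zero in the wrong direction.

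**5. The one misprint.** For 70% against 60% at 30% loss, r = 0.1: SE1 = √(0.21/350) = 0.02449, SE2 = √(0.24/245) = 0.03130, variance = 0.000600 + 0.000980 − 0.000153 = 0.001426, half-width 7.40. The interval is 2.6% to 17.4%. The table prints 17.6%, which is not symmetric about 10.

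**The case against.** Table 4 only illustrates precision. Change between visits is not a numbered objective: primary objective 4 concerns factors that may affect persistence and adherence. Power is stated for a Time 1 cross-sectional comparison, and the Data analysis text names no estimator of change. Adherence among continuers is a legitimate quantity, and the protocol treats persistence and adherence as separate ideas. Eligibility is re-assessed quarterly, so some women may stop because they no longer qualify, and calling them non-adherent has a cost. Figure 2 is not shown; its surviving labels mention a longitudinal sample, so a paired subset may be drawn there. An analysis plan could settle the estimator.

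Much of this stands and limits the point to the between-visit contrast. It does not remove it, because the protocol itself prints a 350-versus-175 (or 245) comparison and gives assessment over time as a purpose of the second sample.

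Several stronger readings are tempting but not supported:

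- **The planned contrast will have the wrong sign.** That needs selection of a strength the protocol does not quantify. In the 50% to 61% illustration the paired change is zero. It becomes a fall only if stopping is itself counted as non-adherence (0.5 × 0.733 = 37% of all women).
- **The Time 2 regression is biased.** The protocol does not say which visit feeds its regression.
- **The covariance term is wrong.** The note to Table 4 can be read as the correlation between the two estimated percentages, for which the term used is right. The other reading moves the 50%/30% limits by about 0.1 point.
- **Counting discontinuers buys precision.** The larger denominator goes with a different rate and a different quantity, so the half-widths are not comparable.

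**Conclusion.** The point holds for the between-visit difference in Table 4. That difference compares all women at Time 1 with continuers at Time 2, and it equals the change among continuers only if continuing is unrelated to Time 1 adherence. Under the assumed selection the spurious shift is about 11 points at a risk ratio of 2 and 17 at a ratio of 3, against tabulated differences of 10 and 20 points. A reversed sign is possible under strong selection but is not shown to be likely. On a paired basis the intervals also widen, from 11.85%–28.15% to 10.47%–29.53% in the protocol's own example. The Time 1 rates and the Time 1 cross-sectional power statement are not affected by this point.

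**What to change.** 1. Define the between-visit change as paired: each continuer's Time 2 result against her own Time 1 result. Recompute the difference block of Table 4 on that basis.
2. Beside it, report Time 2 adherence among all women of known Time 2 status, counting those who meet the section 4.0 discontinuation definition as not adherent. Label it a composite of persistence and adherence. As an example, assume 40% stop and 10% are lost: 30% of 175 continuers is 52.5 women, or 52.5/315 = 16.7%. Taking the 35 lost women as all non-adherent or all adherent gives 52.5/350 = 15% to 87.5/350 = 25%.
3. Apply the composite rule to any regression that uses Time 2 adherence.
4. If the present table is kept, correct 17.6% to 17.4%.

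The protocol's figures support the coding in item 2: with its 17.1-day red-cell half-life, 60 days without drug leaves 2^(−60/17.1) = 8.8% of the level, assuming doses ended when the refill fell due.

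The cost is protocol wording and a recomputed table. No new data are needed, because continuers already have a Time 1 DBS and discontinuation is covered at the second interview. The paired intervals are wider at the table's correlations. The composite merges stopping with low drug level, so show the two parts separately, with reasons for stopping where recorded.

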**Data analysis**

AGYW will be considered adherent if their tenofovir-diphosphate drug levels in DBS exceed 30f/molx106, which is consistent with an average of at least four PrEP doses per week. Thus, adherence measured by dry blood spot is a dichotomous measure (Yes, if drug concentration level exceeds 30f/molx10^6 and No otherwise). We will also examine adherence based on the AGYW self-report and for analysis of concordance between adherence measures (e.g. self-report and drug concentration level-based measures), we will calculate Cohen's kappa coefficient as well as sensitivity, specificity and positive predictive values, which are commonly used to assess the degree of agreement between two binary rates.^[[48]](#endnote-48)^ ^[[49]](#endnote-49)^

Data analysis will be done by study team staff who have both qualitative and quantitative analysis experience and skills. Data analysis of quantitative data will be conducted using SAS, STATA or R. Descriptive statistical analysis including frequencies of responses and distribution will be used to summarize factors influencing PrEP uptake and adherence. Chi-square tests will be employed to make comparisons between groups, such as married and unmarried. Multivariate regression analysis will determine whether differences in adherence rates are associated with any particular contextual co-factors, such as the experience of intimate partner violence, levels of social support, perception of HIV stigma, self-efficacy, depression, alcohol use, etc.

Focus groups and in-depth interviews will be translated, transcribed, and analyzed thematically using qualitative software, such as Atlas.ti. Focus group and in-depth interview analysis will explore factors that facilitate or are barriers to PrEP uptake and adherence for AGYW from the perspective of peers, mentors and health workers (focus groups) and will explore these factors more in-depth in the qualitative interviews with young women who continuer or discontinuer PrEP.

### 4.0 Study procedures

The study procedures involve two one-on-one semi-structured interviews conducted by study staff with the AGYW. These interviews will take not more than 1 hour. The interviews will take place at private spaces in the DREAMS program ‘safe spaces’ or, if preferred by participants, may alternatively be conducted at other community locations, places of residence or the workplace as convenient and desired by the participant.

We will conduct one follow-up visit with each AGYW after an interval of 3 to 4 months. At this visit study staff will conduct a second interview. If the AGYW is continuing with PrEP, questions will focus on adherence and factors that impact adherence. If the AGYW has discontinued PrEP, questions will focus on reasons for discontinuation. Illustrative lines of inquiry for both interviews are outlined below.

We will collect a dried blood spot (DBS) sample from each AGYW who is continuing in the PrEP program at two points in time, separated by an interval of 3 to 4 months. PrEP discontinuation is defined as 60 or more days since due for a PrEP refill, and AGYW reports that she is not currently taking PrEP. Those who have discontinued will participate in the interview only.

A trained HTS (HIV testing services) worker -- trained in research ethics, blood sampling via fingerstick, and interviewing techniques -- will be employed as study staff to take the samples and conduct the interviews.

In addition to the DBS collected from study participants, we will recruit, consent, and collect a DBS from up to 10 HIV+ AGYW who are on ART (TDF) and virally-suppressed to serve as positive controls for the purpose of validating the DBS storage and testing procedures. Because these individuals are virally suppressed from their ART, their DBS test results will show adherent tenofovir levels, assuming an accurate test assay and effective DBS collection, storage, and transfer procedures. Other than the DBS, their age, their length of time on ARTs, and duration of viral suppression (if known), no additional information from these positive controls will be collected. To clarify, these participants are not contributing toward the achievement of the study objectives per se, nor providing data for the analysis, but are critical to validate that the DBS testing results obtained from study participants are accurate measures of PrEP adherence. PATH has a project, called Afya Ziwani, that provides services to HIV+ individuals in Kisumu and Nyamira counties and therefore is able to identify women on ART who, if willing, could serve as positive controls.

*Quantification of PrEP Adherence:* We will measure tenofovir diphosphate (TFV-DP) in finger-prick whole blood dried blood spots. Dried blood spots (DBS) have been demonstrated to be a suitable measure for TFV-DP, as a long-term measure of TDF and PrEP adherence. Approximately 2.5 ml of blood is required for the dried blood spot card.

All drug measurements will be performed at the Program for HIV Prevention and Treatment (PHPT) laboratory at Chiang Mai University (ISO:15189 certified), pharmacology laboratory established by [name] in 2003. The Chiang Mai University laboratory is approved by the Division of AIDS (DAIDS) to perform antiretroviral drug level measurements by liquid chromatography dual mass spectrometry (LC-MS/MS), and is the reference laboratory for IMPAACT and DAIDS studies in Thailand. In accordance with DAIDS polices, the lab participates in the Clinical Pharmacology Quality Assurance and Quality Control Program (CPQA).[^63^](#_ENREF_63) The CPQA program includes regular proficiency testing, external review of SOPs/validation reports, and audits. Drug assays used by the lab are validated based on the US FDA ‘Bioanalytical Method Validation’ guidelines.

This research approach was developed in [name]’s lab at the University of Colorado, and the seminal paper is the following:  Castillo-Mancilla JR, et al. "Tenofovir, emtirictabine, and tenofovir diphosphate in dried blood spots for determining recent and cumulative drug exposure.” In this paper, the authors describe the protocol and validation study for using DBS for the measurement of cumulative TFV-DP. In 2017, [name] and his team spent 2 months as Visiting Scientists in [name] lab learning the protocol for testing TFV-DP from DBS. The [name] lab is now using the same protocol for the DBS testing using dual liquid chromatography mass spectrometry that was pioneered in the [name] lab.  The [name] lab is currently testing DBS samples in the TARGET Study (PI:  [name], who is a co-investigator on the current study), and the quality of results has been excellent.

This lab and the lab in Colorado are the only labs that are measuring tenofovir diphosphate (TFV-DP) in finger-prick whole blood dried blood spots.

*Storage of Samples*: All of the DBS samples will be stored in a local -20 C freezer. The samples will be shipped frozen to the PHPT laboratory in Chiang Mai, Thailand. Once received, the samples will again be placed in a -20 C freezer until the time of testing. The study will develop SOPs for study staff to detail DBS sampling procedures, storage, and transport logistics.

IDIs with PrEP continuers and discontinuers (a subset of survey respondents) will be scheduled following the second quantitative interview, based on timing that is convenient to the participant. The IDIs will last no more than one hour.

Focus group discussions will be conducted at Safe Spaces or other appropriate venue providing participants with adequate privacy. The study will employ a trained facilitator to conduct the focus group discussions. They will be audio-recorded.

### 5.0 Eligibility criteria

Note that DREAMS participants have previously consented to be contacted about possible participation in future studies of this type. The legal age of consent in Kenya is 18 years.

